### **11.7 Safety evaluation**

Check whether there is any adverse event through vital signs, hematological test, serum biochemical test and urinalysis immediately after surgery, at 1 week and 6 weeks after surgery.

## **12. Predicted side effects and precautions for use**

### **12.1 Predicted side effects**

- 1) Side effects associated with general surgery : Abscess, cellulitis, wound, dermal necrosis, swelling, hematoma, cardiovascular disease, hypertension, ischemia, thrombus, embolism, hemorrhage, complications related to anesthesia, pulmonary complications, nerve/muscle damages, etc.
- 2) Side effects associated with the use of anti-adhesion product : Infection, allergic reaction, pain, and inflammatory reaction
- 3) Side effects associated with total thyroidectomy : Hypoparathyroidism, recurrent laryngeal nerve injury, hemorrhage, infection, superior laryngeal nerve paralysis, dyspnea, etc.

In the event of a predicted side effect, record the name and extent of the side effect as an adverse event in the Case Report Form according to the following criteria for mild, moderate and severe.

- Mild : A degree to which a subject can easily endure, without interfered with his/her normal daily life (or function) and with causing minimal discomfort
- Moderate : A degree to which it causes inconvenience to the extent that it significantly hinders the normal daily life (or function) of a subject
- Severe : A degree to which the normal daily life (or function) of a subject is impossible; a degree to which a subject is unable to continuously participate in the study; or a degree to which a subject needs to be treated or hospitalized

### **12.2 Precautions for use of experimental product**

#### **12.2.1 General precautions**

- 1) Read all instructions and precautions for use before using this product. Failure to properly follow the instructions and precautions for use may result in the product not functioning properly or infection or side effects.
- 2) MegaShield is a surgical product, shall be used by specialized medical personnel and shall not be used for any purpose other than its intended use.
- 3) Since this product is sterile, it should be maintained in a sterilized state during the procedure, and expired products should not be used.
- 4) Before use, the contents of the product should be checked. If any signs of damage or moisture appear in the packaging or containers, do not use the product.
- 5) Before the MegaShield solution is injected into the surgical site, the surgeon should remove any remaining liquid, such as cleaning solution, by sucking it with an aspirator.
- 6) If a patient is found to have side effects, follow the "15. Evaluation Standard of Safety Including Side Effects, Its Evaluation Method and Report Method" in this protocol. In addition, hospitals and physicians should take the necessary medical measures for the patient.
- 7) The validity period is one year from the date of manufacture.

12.2.2 Precautions for adverse events which may occur as a result of using the medical device, fatal side effects due to negligence in use, and accidents

- 1) If any damage to the package is found prior to use, the product shall not be used, and the damaged product shall be returned or exchanged by contacting L&C Bio Inc.
- 2) If a product opened prior to transplantation to a patient has been left in a contaminated and non-sterile condition, it should not be used for transplantation and should be returned by contacting L&C Bio Inc. or disposed of appropriately as medical waste.
- 3) Before using this product for transplantation, it is essential that the patient to be transplanted has an allergic reaction to any reagent or solution used in the manufacture of this product.
- 4) This product shall be used within the expiration date indicated on the label, and products that have been expired shall be returned or exchanged by contacting L&C Bio Inc.
- 5) This product shall be stored in a cool, dry place, avoiding direct sunlight, in accordance with the recommended storage conditions.

12.2.3. Use for pregnant women, lactating women, women of childbearing age, newborns, infants, children, and the elderly

This product should not be used if a patient to be transplanted has an allergic reaction to any reagent or solution used in the manufacture of this product, prior to use for transplantation. This product should not be used if a patient, in particular, with reduced immunity has the potential to cause side effects.

#### 12.2.4. Precautions on application

- 1) This product shall be stored and used at room temperature.
- 2) This product is a gamma-sterilized product, it should not be used by re-sterilization, and once opened, it should not be re-sterilized for reuse.
- 3) Each individually packaged MegaShield should be used only for one patient.
- 4) Since this product is disposable, the remaining solution should be discarded after use and should not be reused.

#### 12.2.5. Matters necessary to prevent safety accidents

- 1) This product is produced through the GMP process certified by the Ministry of Food and Drug Safety. Therefore, it is recommended that this product be used in appropriate environments (clean room or operating room) and facilities similar to the manufacturing environment when using this product.
- 2) Be careful not to contaminate the affected area or the treatment area when using this product.

### **12.3 Precautions for use of comparator**

#### 12.3.1 General precautions

- 1) Since this product is sterile, it should be maintained in a sterilized state during the procedure, and expired products should not be used.
- 2) Before use, the contents of the product should be checked. If any signs of damage or moisture appear in the packaging or containers, do not use the product.
- 3) Before the GUARDIX-SG solution is applied to the surgical site, the surgeon should remove any remaining liquid by sucking it with an aspirator.

#### 12.3.2 Precautions for handling

- 1) GUARDIX-SG solution should be stored and used at room temperature.
- 2) GUARDIX-SG solution can be used even when warmed to body temperature and becomes a gel.
- 3) Sterilized GUARDIX-SG is provided and shall not be used after re-sterilization.
- 4) Since this product is disposable, the remaining solution should be discarded after use and should not be reused.

#### 12.3.3 Contraindications

- 1) GUARDIX-SG solution should not be applied to a patient with infected or contaminated surgical site.
- 2) GUARDIX-SG solution should not be applied to a patient who is hypersensitive to its ingredients.

- 3) When GUARDIX-SG solution is used in combination with other anti-adhesion products, absorbable hemostatic agents, or other drugs, its safety and efficacy have not been verified in animal testing.
- 4) The use of GUARDIX-SG solution is not recommended during pregnancy.
- 5) It is recommended to avoid pregnancy until the end of the first menstrual cycle after use of GUARDIX-SG solution.

#### 12.3.4 Predicted side effects

- 1) Infection : Pyrexia, leukocytosis
- 2) Allergic reaction : Generalized rash, dyspnea, edema
- 3) Pain
- 4) Inflammation

## 13 Discontinuation and drop out

### 13.1 Criteria for discontinuation

- 1) Where the principal investigator determines that the situation observed during the clinical trial is unreasonable for continuing the clinical trial
- 2) Where the clinical trial is to be discontinued due to the safety of the investigational product, etc.
- 3) Where the study is temporarily discontinued to deal with an adverse event that has occurred
- 4) Where the used medical device is removed and the study is discontinued to deal with an adverse event that has occurred
- 5) Where the study is discontinued due to the occurrence of a serious adverse event/adverse device reaction

### 13.2 Management of discontinuation

- 1) If the clinical trial is discontinued, the principal investigator shall collect and deliver the Case Report Form, the clinical trial progress status and results of the subject of which have progressed to the point where the study was discontinued to Sponsor. All study-related data (Case Report Form and the investigational product) shall be returned to the sponsor. Subjects whose the clinical trial has been discontinued shall be included in statistical processing for safety and efficacy evaluation.
- 2) If the clinical trial is terminated early or temporarily discontinued, the principal investigator shall immediately inform the subjects and ensure that appropriate measures and follow-up are carried out. And the principal investigator shall notify the Institutional Review Board of that in writing.

### **13.3 Criteria for drop out**

- 1) Where a subject or his/her legal representative requests to stop participating in the clinical trial
- 2) Where surgery, drugs, or other medical devices that may affect the safety or efficacy have been used in combination
- 3) Where serious side effects occur
- 4) Where the treatment method has not been performed properly
- 5) Where a subject fails to comply with the requirements presented in the consent form, thus affecting the evaluation
- 6) Where continuous observation is not possible due to the absence of a subject
- 7) Other cases where the investigator determines that there is a problem in conducting the clinical trial

### **13.4 Management of drop out**

- 1) If a subject is dropped out, record and keep the reason for the drop out and the related data to the clinical trial progressed before the drop out.
- 2) If a subject failed to visit during the study, check the subject's health condition and clarify the reason.
- 3) The subject dropped out shall be included in statistical processing when evaluating the safety and efficacy.

## **14 Evaluation Standard of Efficacy, Its Evaluation Method and Analysis Method (by statistical analysis method)**

The evaluation standard, evaluation method and analysis method of efficacy shall be based on the clinical study procedures published in the Korean Journal of Endocrine Surgery in 2009 [24].

### **14.1 Primary efficacy endpoint**

For the primary endpoint of this clinical trial, score the esophageal movement scores evaluated by marshmallow esophagography at 6 weeks after surgery into four grades (0, 1, 2, and 3). The primary endpoint is evaluated by providing the frequency, proportion, mean, standard deviation, median, minimum and maximum of the esophageal movement scores and by using the one-sided 97.5% confidence interval for the difference in the mean score of the 'esophageal movement' between the two groups (test group - control group) to determine whether the effect of the new treatment is non-inferior to the existing treatment. That is, if the lower limit of the one-sided 97.5% confidence

interval is greater than  $-0.1$ , which is the limits of non-inferiority ( $-\delta$ ), it is judged that 'the test group is non-inferior to the control group.'

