### 8.4. Basis for calculation

Suppose that the esophageal movement score (Marshmallow esophagography score) of the test group (MegaShield) is not lower than that of the control group (Guardix-SG) after thyroidectomy (non-inferiority test). In other words, this study is to test whether the test group is non-inferior to the control group. The null hypothesis is that the test group is not non-inferior in the mean of parameters to the control group, and the alternative hypothesis is that the test group is non-inferior in the mean of parameters to the control group [17].

Null hypothesis  $H_0$  :  $\varepsilon \leq -\delta$  , and

alternative hypothesis  $H_a$  :  $\varepsilon > -\delta$ .

$$n_1 = \frac{2(z_{\alpha/2} + z_{\beta})^2 \sigma^2}{(\varepsilon - \delta)^2}$$

where,  $\alpha$  : significant level     $1 - \beta$  : power,  $\sigma^2$  : variation,

$\varepsilon$  = difference between the means of the esophageal movement scores of the two anti-adhesion products (test group - control group), assuming there is no difference between the two groups ( $\varepsilon=0$ ),

$\delta$  = margin (limits of non-inferiority), 0.1 (the degree to which is regarded to be clinically significant)

To take into account both the existing comparator and placebo effect when setting the limits of non-inferiority, assume that:

'The effectiveness of the new treatment is non-inferior to that of the existing one' and 'the effectiveness of the new treatment is superior to the placebo effect.'

The margin that satisfies the above assumptions is obtained by the following expression:

$$\Delta = \frac{r}{1+r}(\theta_A - \theta_P)$$

For  $r$ , the difference between the active control and placebo is not used as the margin, and  $[0, 1]$  median is given to consider that  $r$  is smaller than the difference. The margin is multiplied by the ratio of  $[0, 1/2]$  to the difference between the historical active control and placebo.

In the previous study [16], the difference in scores between comparator (Guardix) and Placebo is  $2.93 - 2.73 = 0.2$ , so assuming that  $r$  is 1, the margin is  $0.2/2 = 0.1$ .

Assuming that:

$\alpha$  (Significance level) is 5%,

$\beta$  (power 80%) is 0.2,

$\delta$  (margin) is 0.1, and

$\sigma$  (variation) is 0.2,

the sample size is:

$$n_1 = \frac{2(z_{\alpha/2} + z_{\beta})^2 \sigma^2}{(\varepsilon - \delta)^2} = \frac{2(1.96 + 0.84)^2 0.2^2}{(0 - 0.1)^2} = 62.8.$$

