### 11.3 Randomization method

#### 11.3.1 Randomization

For randomization, make sure that subjects are assigned to the test group and the control group at a ratio of 1:1 by the block randomization method. It will be generated using SAS by a statistical expert who is not directly related to the institution. For blinding, before the study is terminated, only a minimum number of personnel who are not directly related to the institution should be able to access to the randomization table and code. Subsequently, the institution shall finally assign a randomization number (3-digit number) to the subjects who meet the inclusion/exclusion criteria through screening. This randomization code, together with the subject identification code specified in 11.2.4, will be used as the subject identification code during the clinical study.

Ex.: Randomization code

[figure not shown]

2nd, 3rd digits – sequentially

1st digit – institution code (Severance 1, Kangbuk Samsung 2, Seoul St. Mary's 3)

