#### 11.4 Independent evaluator's evaluation

The evaluator of the institution who evaluates the esophagography (primary endpoint) and adhesion scores shall conduct and evaluate surveys of esophagography and adhesion scores while being blinded. And the independent evaluator should be blinded to the treatment group assignment of the subjects so that the independent evaluator can make an objective judgment.

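### The primary non-inferiority interval in 14.1 has no institution term, although randomisation and scoring appear to run by institution; adjusting would cost almost nothing and may gain some power

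*Protocol*

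**What the plan says.** - **Analysis (14.1).** The decision rests on a "one-sided 97.5% confidence interval for the difference in the mean score of the 'esophageal movement' between the two groups", test minus control. Non-inferiority is declared if the lower limit lies above -0.1. No model, covariate or stratification factor is named.
- **Randomisation (11.3.1).** The section says that "subjects are assigned to the test group and the control group at a ratio of 1:1 by the block randomization method". It describes the three-digit code as "1st digit – institution code" (three institutions), followed by two digits that run in sequence. It does not use the word stratified.
- **Scoring (11.4).** The blinded scorer is described as "The evaluator of the institution who evaluates the esophagography (primary endpoint) and adhesion scores". No central reading is described.
- **Sample size (8.4).** The calculation uses one overall SD of 0.2, not split into parts within and between institutions, a margin of 0.1, and a true difference of zero ("assuming there is no difference between the two groups").

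**The concern.** A code that starts with the institution and then counts upwards is most naturally read as one block list per institution. Allocation is then close to balanced within each institution, and institution differences cancel out of the treatment comparison. An unadjusted two-group standard error does not take credit for this. It keeps the between-institution variance in the error term, so it overstates the uncertainty of the difference.

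Scoring by each institution's own evaluator is one plausible way for institution means to differ. What is at stake is a little power against a margin of 0.1, and a lower limit that covers slightly more than its nominal 97.5%.

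**Working it through.** **Inputs from the protocol:** margin 0.1, SD 0.2, true difference 0, z = 1.96 and 0.84 (8.4); 63 per group, 70 after 10% dropout (8.4); lower one-sided 97.5% limit (14.1).

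**Assumed input:** s, the share of score variance lying between institutions. The documents give no value. The values 0, 2%, 5% and 10% are used.

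**Step 1: reproduce the plan.** n = 2 × (1.96 + 0.84)² × 0.2² / 0.1² = 62.72 (the protocol prints 62.8). Both round up to 63; 63 / 0.9 = 70 per group, 140 in total. The plan's size reproduces and does not rely on adjustment.

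**Step 2: standard error.** Unadjusted SE = 0.2 × √(2/63) = 0.0356. With institution in the model, the residual SD is 0.2 × √(1 − s), so the unadjusted SE is too large by the factor 1/√(1 − s).

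**Step 3: power and error rate.** With balance within institution, the true SE of the difference is 0.0356 × √(1 − s) in both analyses. The unadjusted analysis still uses 0.0356 for its interval. Since 0.1 / 0.0356 = 2.806:
- unadjusted power = Φ((2.806 − 1.96) / √(1 − s))
- adjusted power = Φ(2.806 / √(1 − s) − 1.96)
- unadjusted one-sided type I error = 1 − Φ(1.96 / √(1 − s))

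| s (assumed) | SE too large by | Half-width, adjusted | Power, unadjusted | Power, adjusted | Gain (points) | Type I error, unadjusted |
|---|---|---|---|---|---|---|
| 0 | 0% | 0.070 | 80.1% | 80.1% | 0 | 2.5% |
| 2% | 1.0% | 0.069 | 80.4% | 80.9% | 0.5 | 2.4% |
| 5% | 2.6% | 0.068 | 80.7% | 82.1% | 1.4 | 2.2% |
| 10% | 5.4% | 0.066 | 81.4% | 84.1% | 2.7 | 1.9% |

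The unadjusted half-width is 1.96 × 0.0356 = 0.070 in every row.

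**Step 4: simulation check.** 20,000 runs, 126 analysed, three institutions balanced within institution, t-based limits.

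| s (assumed) | Power, unadjusted | Power, adjusted | Type I error, unadjusted |
|---|---|---|---|
| 0 | 79.6% | 79.6% | 2.6% |
| 5% | 79.9% | 81.4% | 2.3% |
| 10% | 80.7% | 83.6% | 2.0% |

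The adjusted type I error stays at about 2.5 to 2.6%. The gains of about 1.5 and 3 points agree with the formulas. Unequal institution sizes (80, 26 and 20) gave nearly the same power for the unadjusted analysis.

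The formulas and the simulation treat the score as normal with constant variance. A 0 to 3 scale near its ceiling would change the exact figures but not the direction.

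**The case against.** **It belongs in the SAP.** Section 14.1 is silent on the model behind the interval, covariates are often fixed in the SAP, and the SAP is not shown. This limits how strongly the point can be put: the protocol does not rule out adjustment, and an unseen SAP may already contain it. But 14.1 does fix the estimate, the interval and the decision rule, and as written these describe a plain two-group difference. Suggesting a better comparison in its place is still fair.

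**The premises are inferred.** Stratification is read from the code format, and one evaluator per institution from the wording of 11.4. Both readings are natural, but neither is stated.

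**Institution differences may be small.** A reader might infer that they are likely because scoring is local. The documents do not show this, and the grades follow 30-second cut-offs common to all institutions (11.5). The low end of the range is also the more realistic. Suppose all scores are 2 or 3 with a mean of 2.93, the comparator's figure quoted in 8.4. Then 7% score below 3. Three equal institutions would need rates of 0%, 7% and 14% to reach a 5% share; rates of 3%, 7% and 11% give 1.6%.

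**A larger SD.** A reader might enter an SD above 0.2 to argue that a trial already short of power loses more. Section 8.4 states 0.2, at which 63 per group gives 80.1%. Whether 0.2 is attainable is a separate question, and this point does not depend on it.

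**Baseline covariates.** A reader might also want the screening swallowing items in the model. The documents give no link between those items and the six-week grade, define no sum of them, and already use them as the reference for change in the secondary endpoint. That extension is not supported.

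**Conclusion.** The point holds as a nearly free improvement, with moderate confidence. If the block lists run by institution and institutions differ, the interval in 14.1 is somewhat too wide. Under assumed shares of 2% to 10% the excess in SE is 1.0% to 5.4%, and the power forgone at the protocol's SD is about half a point to 3 points. At a share of zero nothing is lost either way.

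A reader might infer that the interval is invalid because its coverage is not exactly 97.5%. The documents do not support that: the departure is on the safe side, the rate of false non-inferiority claims is at or below 2.5% apart from simulation noise, and 63, 70 and 140 stand without adjustment. Nor can it be said that precision is certainly lost, since that depends on a variance share the documents do not give.

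**What to change.** In 14.1, and in the SAP to match, base the lower one-sided 97.5% limit on the institution-adjusted mean difference, either from a linear model with arm and institution or as a stratum-weighted difference. Keep the unadjusted difference as a supporting result. In 11.3.1, state whether the block lists are stratified by institution. If the SAP already adjusts, 14.1 should say so.

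The cost is one sentence in each place and two degrees of freedom for three institutions; the sample size does not change. The choice should be fixed before unblinding, because picking between adjusted and unadjusted limits afterwards would be open to challenge.

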#### ※Marshmallow esophagography

First, measure the esophageal passage time of the marshmallow in the prone position, and classify it into normal and abnormal based on 30 seconds. When the marshmallow gets stuck in a part of the esophagus and does not move for more than 30 seconds, it is defined as an impaction. If an impaction has occurred in the prone position, ask the patient to change the posture to standing position and swallow his/her saliva, then observe the movement of the marshmallow in the esophagus. With this test, evaluate the marshmallow's passage pattern in the esophagus by dividing them into 4 grades as shown in the following table.

| Score | Definition | Esophageal passage time of marshmallow                                                                       |
|-------|------------|--------------------------------------------------------------------------------------------------------------|
| 3     | Normal     | Passed through the esophagus within 30 seconds in the prone position                                         |
| 2     | Minor      | Passage time exceeds 30 seconds in the prone position; and passed within 30 seconds in the standing position |
| 1     | Moderate   | Impacted in the prone position; and passage time exceeds 30 seconds in the standing position                 |
| 0     | Severe     | Impacted in both the prone and standing positions                                                            |

